**Appendices**			
Informed consent materials	32	Model consent form and other related documentation given to participants and authorised surrogates	In the attachment
Biological specimens	33	Plans for collection, laboratory evaluation, and storage of biological specimens for genetic or molecular analysis in the current trial and for future use in ancillary studies, if applicable	N/A

### Study setting

The research will include individuals aged 65 years or older, of all genders, who meet the study’s inclusion criteria. Therapy sessions will be conducted individually and in person, in offices suited for psychological practice. Participants residing in senior housing will have the option, subject to agreement with their institution, to have sessions conducted in their facilities [22,23]. Each session will last one hour and occur weekly over a three-month period, resulting in a total of 12 sessions per participant, in accordance with the EFT protocol for resolving emotional injuries established by Meneses and Greenberg (2019), with adaptations presented below.

At the conclusion of the designated sessions, in accordance with the study plan and study procedures (Fig 1), assessment data will be gathered in paper format. When a participant misses a session, it will be rescheduled as soon as possible. The questionnaires will be completed after the sessions. If necessary, a member of the research team will assist participants in completing them in order to prevent fatigue. In all cases, the questionnaires (with their number based on previous study protocols involving older adults [32]) will be administered in distinct and varied sessions, with clear instructions, scheduled breaks, and diverse formats to minimize fatigue — regardless of significant variations in the participants’ individual schedules [29,32]. All collected data—including attendance records and dropouts—will be analyzed in accordance with the study protocol (intent-to-treat analysis versus treatment completers analysis), not only to inform the current analysis but also to support the design of future studies. It is expected that at least 70 participants will complete the intervention (more on this below), and any reasons for dropout will be systematically documented. Regarding the secondary objective, which focuses on the analysis of outcome variables, particular attention will be given to the data from participants who complete the full intervention (completers).

**Fig 1 pone.0345792.g001:**
[figure not shown]
Study procedures.

If participants require extended support, provisions for longer therapy sessions may be made as a clinical decision [24–26]. For those who exceed the twelve-week period due to clinical reasons, the analysis will be split into two parts: one including all participants up to week 12, and a separate analysis assessing the impact of extra weeks for these participants only [22,23]. The current study protocol has been submitted to and approved by the Ethics Committee of the University of Maia, granting approval under the number 40/2022 (see Supporting Information: Ethics committee (in English and Original).

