## Abstract

Over recent decades, Emotion-Focused Therapy, aging, and forgiveness have garnered significant attention in the field of psychology. However, there is a lack of studies on Emotion-Focused Therapy and forgiveness specifically tailored for older adults. This article presents a protocol designed to assess the feasibility and acceptability of a randomized controlled trial of Emotion-Focused Therapy aimed at resolving emotional injuries in individuals aged 65 and older, within the context of interpersonal offenses. Feasibility will be evaluated through recruitment and retention rates, as well as adherence to the intervention protocol. Acceptability will be assessed based on perceived treatment credibility, participants’ expectations regarding outcomes, levels of engagement, and overall satisfaction with the intervention. The study is structured as a two-arm, parallel-group randomized trial with a waiting list control. We propose recruiting a sample of 70 participants, randomly assigned to either an immediate intervention group, which will receive Emotion-Focused Therapy over twelve weekly sessions, or a control group that will receive the same therapy after a twelve-week waiting period. Data will be collected in the beginning, middle, and at the end of therapy, and in two planned follow-ups (three and six months after therapy). Once this protocol is implemented, if the therapy proves to be feasible, acceptable, and shows promising results, the findings will inform a large-scale randomized clinical trial to advance the understanding of this treatment for individuals aged 65 + .

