### Participants

Our feasibility study will include a minimum total sample of 70 older participants, with 35 randomly allocated to the intervention group (IG) and 35 to the waitlist control group (CG) [22,29]. Although feasibility studies do not require large samples [33], they should adequately represent the target population and be sufficiently large to fulfill the study’s objectives. Authors [33,30,31] agree that feasibility RCTs typically recruit between 24–50 participants per arm on average, with the exact number depending on the specific aims and objectives of the study. Larger sample sizes may be necessary for more complex or ambitious goals (in accordance with the G*Power requirements for comparing two groups) [33,30,31].

Given the exploratory nature of our study—aimed at evaluating the feasibility and acceptability of the therapy, as well as obtaining preliminary insights into its potential effectiveness among the participants involved, rather than establishing causality or generating generalizable results—we determined that a sample size of 70 participants would be appropriate. This decision was informed by precedents in comparable feasibility studies [22,29,34], as well as by practical considerations such as recruitment capacity, budgetary constraints, and the minimum sample size required to adequately address feasibility-related objectives [35]. Based on all of this, we propose to include 80 individuals in our study to ensure that at least 35 participants complete each comparison group (minimum N = 70). Therefore, in line with other studies, an additional 15 percent of participants will be recruited to account for typical dropout rates [9,13].

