### Data collection

As illustrated (Fig 2), various measures will be administered throughout the study—from participant selection to the two planned follow-up assessments. To minimize the burden on participants, questionnaires scheduled for completion at the end of the therapy will be distributed either during the final session or at home between sessions. The questionnaires will be returned in sealed envelopes to the therapists, who will then hand them over to the psychologist responsible for the evaluation process. This independent psychologist will also conduct the initial assessment for study integration and the final qualitative interview [22,29].

To efficiently assess whether potential participants meet the study criteria, eligible individuals will undergo the Structured Clinical Interview for DSM-5—Research Version (SCID-5-RV) [59] and the Montreal Cognitive Assessment (MoCA) [37,38]. Additionally, socio-demographic data, including age, gender, occupation, religious beliefs, current medications, and details regarding the interpersonal offense or emotional injury experienced, will be collected at the outset [22,25,34].

After participants are assigned to their respective groups, three assessment points will be established: before therapy begins, at the sixth session, and at the final session. These assessments will focus on Forgiveness, Letting Go, Quality of Life, and Depression. Before therapy commences, the CEQ will also be administered. Following each session, the Satisfaction Therapy Module and Homework Evaluation will be conducted. Upon completion of therapy (t3 and t5), the CCIP will be administered. To ensure adherence to the therapy protocol, sessions will be recorded for subsequent supervisory evaluation [22,29,34]. Research assistants will provide updates and reminders for follow-ups via telephone and/or email.

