### Statistics and data analysis

#### Quantitative analysis.

Quantitative data analysis will be conducted using SPSS version 29.0 for Windows [60]. Given the study’s exploratory character, particularly with regard to its secondary objective—namely, the study of treatment outcomes—the primary focus is not to test formal hypotheses but rather to provide an initial descriptive overview of the data [22,25]. Accordingly, we have chosen to employ descriptive statistics such as means, standard deviations, frequencies, and percentages to summarize the results. By prioritizing descriptive statistics, we seek to maintain methodological rigor while offering meaningful insights that may inform future, more comprehensive and definitive investigations [35,34].

The ratio of individuals who accepted the invitation to participate in the study relative to the total number of formal invitations sent will help determine the recruitment size. It is anticipated that accurately quantifying the total number of individuals reached through various channels may prove challenging. Additionally, the ratio of participants who complete therapy compared to those who initially commenced it will offer insights into retention rates. Furthermore, the completion rates of the questionnaires will serve as an indicator of their feasibility. Other measures, including assessments of acceptability and feasibility—such as the CEQ, CCIP, Session Satisfaction Module, and Homework Evaluation—will be assessed through exploratory data analysis [22,25,29,34].

To identify and quantify potential associations among the different variables for the main trial, Pearson correlations will be performed to analyze observed changes over time in the control group for all outcome variables. The calculation of the sample size for a future large-scale randomized controlled trial will be guided by the statistical power required to detect clinically meaningful effects, rather than by the provisional estimates derived from this feasibility study [35].

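### The extra-weeks analysis is described as an assessment of impact, but a group extended by clinical decision, analysed alone with no comparator, cannot show the impact of extra therapy

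*Protocol article*

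**What the plan says.** The relevant text is in the protocol article, Method, Study setting, in the paragraph after Figure 1. Extension is left to clinical judgement: "If participants require extended support, provisions for longer therapy sessions may be made as a clinical decision". The analysis then follows: "For those who exceed the twelve-week period due to clinical reasons, the analysis will be split into two parts". The first part is "one including all participants up to week 12". The second is "a separate analysis assessing the impact of extra weeks for these participants only". The text gives no extension threshold, no outcome measure, no time points and no comparison group for the second part.

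Three other places bear on it:

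- The Abstract describes the comparison arm as "a control group that will receive the same therapy after a twelve-week waiting period".
- Data collection says that "three assessment points will be established: before therapy begins, at the sixth session, and at the final session"; the Abstract and Study design add follow-ups at three and six months after therapy.
- Quantitative analysis says of the outcomes that "we have chosen to employ descriptive statistics such as means, standard deviations, frequencies, and percentages to summarize the results", and Participants says that the study does not set out to establish causality.

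**The concern.** The sentence fixes both a target (the impact of the extra weeks) and a population (the extended participants alone). That target cannot be reached in that population. People enter the group because someone judged that they needed more support, and nobody comparable who stopped at week 12 is in the analysis. Whatever change is seen has several possible causes that the data cannot separate.

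The likely error is in one direction. If the decision to extend is related at all to a passing low point, the expected later change is favourable even when the extra weeks do nothing. Natural recovery and late benefit from the first twelve sessions would push the same way. A reader planning the main trial could take such a change as support for a longer therapy, although the study has not tested that. The wording also conflicts with the protocol's own descriptive, non-causal stance.

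**Working it through.** The plan gives no figure for this analysis, so there is none to reproduce. The check has two steps.

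**Step 1: does the design allow a controlled contrast?**

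- *Untreated controls after week 12:* none. The waitlist arm begins therapy when its wait ends.
- *Randomised extension:* none. Extension is a clinical decision.
- *Participants who stopped at week 12:* excluded by the restriction to the extended participants. Including them would still compare groups that differ by clinical need.
- *What is left:* change within the extended participants. The plan does not say this; it follows from the stated population and the descriptive methods.

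**Step 2: how large could regression to the mean be if the extra weeks have no effect?**

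All three inputs are assumptions, because the documents give none:

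- f: share of participants extended, 10–30%.
- ρ: correlation between the week-12 score and the later score, 0.5–0.9.
- g: correlation between the decision to extend and the week-12 score. g = 1 means that the worst scorers are extended; g = 0.5 is a loose link.

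Scores are taken as normal, with no true change, and the decision is taken to be related to the later score only through the week-12 score. The expected apparent improvement in SD units is

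g × (1 − ρ) × φ(z)/f, where z is the (1 − f) quantile of the standard normal and φ its density.

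The factor φ(z)/f is the mean distance of the worst fraction f from the centre: 1.755 for f = 10%, 1.400 for 20% and 1.159 for 30%. For example, with f = 20%, ρ = 0.8 and g = 1, the result is 1 × 0.2 × 1.400 = 0.28 SD.

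| Selection | f | ρ = 0.5 | ρ = 0.7 | ρ = 0.8 | ρ = 0.9 |
|---|---|---|---|---|---|
| Worst scorers (g = 1) | 10% | 0.88 | 0.53 | 0.35 | 0.18 |
| Worst scorers (g = 1) | 20% | 0.70 | 0.42 | 0.28 | 0.14 |
| Worst scorers (g = 1) | 30% | 0.58 | 0.35 | 0.23 | 0.12 |
| Loose link (g = 0.5) | 20% | 0.35 | 0.21 | 0.14 | 0.07 |

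A simulation of 20,000 trials took 35 treated participants (the planned arm size) and extended the worst 7, which is 20%. With no effect of extra therapy, the mean of the extended group improved in 97% of trials at ρ = 0.5, 93% at ρ = 0.7 and 88% at ρ = 0.8. The average gains were 0.68, 0.41 and 0.27 SD, close to the formula.

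The same simulation with the 7 chosen on a stable true score, unrelated to measurement error or passing fluctuation, gave an average change of about 0 and improvement in about 50% of trials. Regression to the mean is therefore conditional on how the decision is made. The missing comparator is not: passing time and delayed effects stay mixed in under any selection rule.

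**The case against.** The strongest reply is that the point reads too much into one sentence. Four parts of it stand.

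- **The contrast is not named.** A reader might infer that the plan specifies a before-after comparison. It does not; within-person change is inferred from the population.
- **The selection rule is not score-based.** A reader might infer that the worst scorers at week 12 are the ones kept on, so that regression to the mean is bound to look like benefit. The text speaks only of clinical need and a clinical decision. The artefact can be near 0, and the strict worst-scorer figures are the upper end of the range.
- **The main analysis is protected.** The analysis of all participants stops at week 12, so data from the extra weeks do not contaminate it.
- **The stated consequences are limited.** Outcomes are exploratory and reported descriptively. Progression criteria rest on credibility and expectancy, session satisfaction, recruitment, retention, questionnaire response and homework. The main trial's sample size is not to be guided by estimates from this study. A reader might infer that the result will set a longer therapy for the main trial, but no passage says so.

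Two parts do not stand. The general disclaimer about causality does not cure a specific promise to assess impact; the two statements conflict. Nor is this a detail that a fuller plan could supply: no choice of measure or time point gives an estimate of impact while the analysis stays confined to the extended participants.

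**Conclusion.** The point holds as a fault of wording and inference, at low severity. The promised analysis cannot estimate the impact of extra weeks, because the group is selected by clinical decision and has no comparator after week 12. That conclusion follows from the text and needs no numerical assumption.

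The size of the bias cannot be computed from the documents. Regression to the mean alone contributes from about 0 to 0.88 SD, depending on the assumed extension share, score correlation and strength of the link between score and decision. The documents do not support the stronger claim that it will by itself produce an apparent benefit. The group would also be small: 10–30% of 70 participants is 7 to 21 people.

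**What to change.** Replace the promise to assess the impact of extra weeks with a descriptive report of the extended participants: how many, the reasons, the extra sessions received, and their scores at week 12 and at the end of the extension. Add that change in this selected, uncontrolled subgroup is not an estimate of the effect of extra therapy and will not be used to choose the therapy length for the main trial. Leave the all-participant week-12 analysis as planned.

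This report needs a score at week 12 and another at the end of the extension. Data collection ties the third assessment to the final session, and Study setting speaks first of longer sessions and then of extra weeks. These statements should be reconciled so that the timing for extended participants is clear.

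The cost is a sentence or two of protocol text before recruitment starts and, if the week-12 score is not otherwise taken, one more set of outcome questionnaires for the few people extended. What is given up is a claim about impact that the data could not support.

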### Participants

Our feasibility study will include a minimum total sample of 70 older participants, with 35 randomly allocated to the intervention group (IG) and 35 to the waitlist control group (CG) [22,29]. Although feasibility studies do not require large samples [33], they should adequately represent the target population and be sufficiently large to fulfill the study’s objectives. Authors [33,30,31] agree that feasibility RCTs typically recruit between 24–50 participants per arm on average, with the exact number depending on the specific aims and objectives of the study. Larger sample sizes may be necessary for more complex or ambitious goals (in accordance with the G*Power requirements for comparing two groups) [33,30,31].

Given the exploratory nature of our study—aimed at evaluating the feasibility and acceptability of the therapy, as well as obtaining preliminary insights into its potential effectiveness among the participants involved, rather than establishing causality or generating generalizable results—we determined that a sample size of 70 participants would be appropriate. This decision was informed by precedents in comparable feasibility studies [22,29,34], as well as by practical considerations such as recruitment capacity, budgetary constraints, and the minimum sample size required to adequately address feasibility-related objectives [35]. Based on all of this, we propose to include 80 individuals in our study to ensure that at least 35 participants complete each comparison group (minimum N = 70). Therefore, in line with other studies, an additional 15 percent of participants will be recruited to account for typical dropout rates [9,13].

Therefore, considering the study’s objectives and similar methodological designs [22,29,34], our eligibility criteria include: being 65 years of age or older; having experienced an interpersonal offense; residing either at home or in a senior residence; stable use of prescribed psychotropic medication—defined as no changes in type, dosage, or frequency within the 8 weeks preceding study enrollment; a score of ≥ 26 on the Montreal Cognitive Assessment (MoCA); and fluency in either Portuguese or English. Exclusion criteria include: reporting an offense that occurred less than one year prior; the presence of severe emotional injuries (e.g., history of domestic, geriatric violence or abuse); psychiatric disorders (that would require a marked divergence in the treatment protocol), diagnosed according to DSM-5 criteria following a structured clinical interview (SCID-5-RV) conducted by a qualified professional; active suicidal ideation or parasuicidal behavior; the recent loss of a close family member (within the past two years); current participation in other therapeutic interventions or clinical studies; ongoing alcohol or drug abuse; cohabitation with another study participant; and frequent hospitalizations—defined as three or more admissions in the past 12 months, as documented in medical records [22,29,34].

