## Method

### Study design

The present publication is a Study Protocol, in the form of a feasibility study. This feasibility protocol is a two-arm, parallel, double-blinded, RCT aimed at informing a future trial assessing the effectiveness of EFT for resolving emotional injuries in older adults (aged above 65) in the context of interpersonal offenses.

This protocol has been registered on the ClinicalTrials.gov registry with number NCT06679452 (see section Ethics approval, below, for further details). The study plans to recruit 70 participants, with half randomly assigned to the EFT intervention and the other half placed on a waiting list to begin therapy after three months, during which they will be assessed [27]. Our chosen sample size aligns with previous similar studies [30,31]. Typically, for studies with two groups, the initial sample size should be adjusted to ensure an adequate number of completers (e.g., recruiting 40 to retain 30) [30,31]. Unlike randomized controlled trials, such feasibility studies do not require power calculations for effectiveness and instead focus on practical metrics, such as the ability to recruit a specified number of participants per month [30,31] (see more below). The recruitment process (which has not yet started) is planned for 2026, contingent upon securing funding. Following the two-month recruitment period, we anticipate initiating data collection. Subsequently, after a nine-month period, we foresee the presentation of results in a third phase. Data will be collected at the beginning, midway, and end of the therapy, as well as three and six months post-therapy (follow-ups). The study follows SPIRIT guidelines and CONSORT standards [28], consistent with prior research (Table 1) [22,29].

**Table 1 pone.0345792.t001:** SPIRIT checklist.

Section/item	Item N.º	Description	Addressed on page number
Administrative Information:			
Title	1	Descriptive title identifying the study design, population, interventions, and, if applicable, trial acronym	1
Trial registration	2a	Trial identifier and registry name. If not yet registered, name of intended registry	4
	2b	All items from the World Health Organization Trial Registration Data Set	N/A
Protocol version	3	Date and version identifier	2025
Funding	4	Sources and types of financial, material, and other support	N/A
Roles and responsibilities	5a	Names, affiliations, and roles of protocol contributors	1
	5b	Name and contact information for the trial sponsor	1 [contact]

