### Progression criteria

This study protocol will be developed for broader research based on the assessment of its acceptability and feasibility. Regarding the CEQ measure, the study will proceed without changes if the result is ≥ 6 on a 9-point Likert scale. The study will also progress without changes in the Session Satisfaction Module if the result is ≥ 3 on a 5-point Likert scale [22]. For recruitment, the progression criterion will be a rate of 75–100% of the sample size [61]. The criterion for retention level will be a rate >80% [36]. The progression criterion for the questionnaires will be a response rate >90%. For homework assessment, a score of ≥ 3 on a 5-point Likert scale will be required [22,29].

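### The sample size is not one number: 70 is the figure recruited, allocated and completing, 80 is the figure included, and the recruitment criterion has no fixed base

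*Protocol article*

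**What the plan says.** The article gives the size of the trial in several places.

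- Abstract: "We propose recruiting a sample of 70 participants".
- Study design: "The study plans to recruit 70 participants, with half randomly assigned to the EFT intervention".
- Participants, opening: a minimum total of 70, "with 35 randomly allocated to the intervention group (IG) and 35 to the waitlist control group (CG").
- Participants, end: "we propose to include 80 individuals in our study to ensure that at least 35 participants complete each comparison group (minimum N = 70"), followed by the reason, "an additional 15 percent of participants will be recruited to account for typical dropout rates".
- Study setting: "It is expected that at least 70 participants will complete the intervention".
- Discussion, limitations: the sample size is given as N = 70.

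Progression criteria then uses the term without a number. For recruitment, "the progression criterion will be a rate of 75–100% of the sample size".

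**The concern.** The figure 70 has three roles: people recruited, people allocated and people completing. These coincide only if nobody drops out, and the Participants section plans for dropout by including 80. A reader cannot tell whether 70 or 80 people will be randomised.

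The step from 70 to 80 also looks reversed. Dropout acts on those who enter, so covering a loss of proportion d means dividing the completer target by (1 − d). Multiplying by (1 + d) gives too few.

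Recruitment is one of the feasibility indicators under the primary objectives, and its progression threshold is a percentage of the sample size. With two candidate sample sizes, the pass mark is not settled before the data are seen.

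**Working it through.** **Inputs.** Completer target: 70, or 35 per arm (Participants). Number included: 80 (Participants). Allowance: 15%, worded as extra recruitment for typical dropout (Participants). Number recruited elsewhere: 70 (Abstract, Study design). Recruitment threshold: 75% (Progression criteria). Assumption: the 15% is read as the dropout rate, because the article gives no separate rate.

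**1. Reproducing the 80.** 70 × (1 + 0.15) = 80.5, given as 80. The plan's figure is therefore an add-on to the completer target.

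**2. What 80 deliver at 15% dropout.** 80 × (1 − 0.15) = 68, or 34 per arm.

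**3. What the target needs at 15% dropout.** 70 / 0.85 = 82.4. Per arm, 35 / 0.85 = 41.2, so 42 per arm and 84 in total.

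**4. Range over the unstated rate, 80 included.**

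| Dropout | Expected completers |
|---|---|
| 12.5% (= 1 − 70/80) | 70 |
| 13.0% (= 1 − 1/1.15, the rate a 15% add-on offsets) | 69.6 |
| 15% | 68 |
| 20% | 64 |

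**5. If 70 are recruited.** 70 × 0.85 = 59.5, about 60 completers or 30 per arm. Reaching 70 would need zero dropout.

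**6. Whether 80 make the target certain.** Take 40 per arm with independent dropout.

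- At 15% dropout, the binomial probability of at least 70 completers in total is 0.33, and of at least 35 in both arms 0.19.
- At 12.5% dropout, the two probabilities are 0.58 and 0.38.
- With 84 randomised at 15% dropout, they are 0.73 and 0.50.

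Inflating by an expected rate does not guarantee a minimum, whichever formula is used.

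**7. Recruitment criterion.** 0.75 × 70 = 52.5, so 53 recruits pass. 0.75 × 80 = 60. For example, 59 recruits are 59/70 = 84% (pass) or 59/80 = 74% (fail). The outcome depends on the base for every count from 53 to 59.

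**The case against.** Several points on the other side carry weight.

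- **The 15% is not stated to be a dropout rate.** It is the recruitment add-on, and the rate itself lies in cited sources. At 12.5% dropout, 80 are exactly enough in expectation. This stands: the claim that the inflation is the wrong way round is conditional on the reading, although that reading is the natural one.
- **The shortfall is small.** It is two completers in a study that disclaims a power calculation (Study design) and analyses outcomes descriptively (Quantitative analysis). The article calls 24–50 per arm typical, and 34 and 35 both fall inside that range. This stands, and it limits the severity.
- **The recruitment base can be inferred.** Participants and the Discussion both use the term sample size for 70, which points to a pass mark of 53. This stands in part. The inference is reasonable, but 80 is the number the plan says it will include, and the criterion names neither.
- **The word minimum softens the 35 + 35.** It does, but it does not soften the Abstract or Study design, which plan to recruit 70.

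A reader might also infer that the retention criterion ("The criterion for retention level will be a rate >80"%) contradicts the completer target, since 70 of 80 is 87.5%. The documents do not support that. A go threshold below the planning target is normal in a feasibility study. Quantitative analysis also defines retention among those who started therapy, which is a different denominator from those recruited or randomised.

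**Conclusion.** The contradiction holds and needs no assumption: 70 recruited, 35 + 35 allocated, 80 included and at least 70 completing cannot all be true if anyone drops out. The arithmetic point is secondary and conditional. If 15% is the dropout rate, 80 give 68 expected completers, and a target of 70 with equal arms needs 84 randomised. The promise that 80 secure 35 completers per arm is too strong at any of the dropout rates considered.

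The practical consequence is the recruitment criterion, where the pass mark is 53 or 60 and the decision is open for 53 to 59 recruits. A reader might go further and conclude that the study is too small or that its conclusions are compromised. Nothing in the documents supports that, because no hypothesis test or power figure rests on these numbers. This is a consistency correction to make before recruitment begins, not a flaw that invalidates the design.

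**What to change.** Use one set of figures throughout.

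- State one number randomised: 80, 40 per arm.
- State one explicit dropout rate.
- Give the completers that follow as an expected number: 68 (34 per arm) if the rate is 15%. Put this in place of the assurance in Participants and the expectation of at least 70 completers in Study setting.
- Align the Abstract, Study design, Study setting, Participants and Discussion with these figures.
- In Progression criteria, name the denominator for recruitment in advance. With the planned number randomised as the base, the pass mark is 60 of 80.

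If the investigators prefer to keep 35 completers per arm as the expected number at 15% dropout, the number randomised becomes 84.

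The cost is wording in six places, a slightly less favourable completer count (68 instead of 70) and a stricter recruitment pass mark than 53. The article says recruitment has not started, so no data are affected.
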